** Secondary objective: Differences between state and federal audits**	
H9	The federal auditor (ASF) yields more observations and more
	refunds to the federal treasury than state auditors (EFSL)
H10	The ASF yields more severe observations and opinions than EFSL
** Tertiary objective: Interactions with local accountability system**	
H11	Municipal administrators in treated municipalities have different
	expectations about future political appointments
H12	Municipal administrators in treated municipalities have different
	expectations about career prospects
H13	Municipal administrators in treated municipalities perceive the
	ASF as a more important principal
H14	State governors compensate audited municipalities for refunds to
	the federal government

This table lists the pre-specified hypotheses that will be tested to help meet the study objectives.

### Policy context

Mexico’s municipalities provide basic public services like drinking water, sanitation, improved road surfaces, and electricity, to 113 million citizens, though access to these services remains uneven across, and within, Mexican municipalities. Improving access of marginalized populations to basic municipal public services is a key element of Mexico’s National Development Plan 2007–2012 [35]. The main instrument available to the Federal Government to achieve this goal is public spending, including earmarked federal grants. For example, the federal Contribution Fund for Social Infrastructure (FISM, in Spanish) provides grants for municipal investments in basic public service infrastructure benefiting local marginalized populations. In FY 2009 it financed one-third of all basic public investment in municipalities, or some 100,000 individual investments [36]. However, the reliance on federal transfer schemes as the key instrument for improving access to public services is not without risks. Municipalities’ ability to identify marginalized communities, diagnose their basic public service needs, propose policy solutions, and implement them is weak. Moreover, the use of federal funds for purposes unrelated to the development of marginalized areas, embezzlement, and corruption are a problem [36–38]. The principal mechanism by which the Federal Congress oversees local governments’ use of federal resources is the national program of audits, directed by the Superior Federal Auditors (ASF, in Spanish) in coordination with the Superior Audit Entities of States (EFSL, in Spanish).

The AUDIT study explores the role that audits play in local accountability systems for infrastructure investments financed by the FISM grant program. The study is based on a field experiment we conducted in partnership with Mexico’s Superior Federal Auditor.

## Methods/Design

### Trial design

The AUDIT study is a block randomized, three-arm parallel group, exploratory trial on a convenience sample of 85 municipalities in Mexico. Blocking was done by state across 17 states, with five municipalities per block. Using non-uniform random assignment and a 1:1:3 blocking ratio we assigned one municipality per block to be audited by the ASF, another by the EFSL, and the remaining three municipalities to the control condition (no intervention). Our reporting of the trial design follows the CONSORT 2010 Checklist [39, 40] (See Additional file 1). The trial received an ethics approval by Yale University’s Human Subjects Committee (ref: 1106008610), and is registered with the International Standard Randomised Controlled Trial Number Register (ISRCTN22381841) and the Experiments in Governance and Politics Network (No:20121031). All end line survey participants are required to give informed consent.

### Participants

Inclusion criteria for participation were designed so as to minimize disruption to the Annual Program of Audits directed by Superior Federal Auditors (ASF, in Spanish) in coordination with the Superior Audit Entities of the States (EFSL, in Spanish) [41]. The study focuses on audits of municipalities’ use of grants from the federal Contribution Fund for Social Infrastructure (FISM, in Spanish). This fund provides grants for municipal investments in basic public service infrastructure benefiting local marginalized populations. The ASF determines which federal programs and recipient entities will be audited and, with regards to FISM related audits, it can also choose to perform the audit itself or request the relevant state EFSL perform it. Against this background the specific inclusion criteria are as follows:

*Stage 1* From the universe of 2,440 municipalities located in 31 states select: States with more than 20 municipalities;Municipalities with FISM transfers in 2010 of 10 million pesos or more;Municipalities not audited in the previous two years (2009, 2010);Municipalities not amongst the 43 pre-selected by the ASF for the 2011 National Program of Audits.

***Stage 2*** From this selection of 767 municipalities located in 21 states select: States with 5 or more municipalities;For each state, rank municipalities in decreasing order of FISM transfers and choose by state the five municipalities with ranks 6 to 10.

The first stage of the selection process of our convenience sample guarantees that our experimental sample includes municipalities that are of relevance to the ASF in terms of the amount of transfers received through the FISM transfer scheme. The second stage of the selection process ensures we have 5 municipalities per state in the experimental group; that our experimental group includes municipalities that are unlikely to have been audited since 1998, when the current audits to FISM expenditures began; and that, within states, municipalities in our sample are similar in terms of the amount of transfers received through the FISM scheme. The final selection includes 5 municipalities in each of 17 states for a total experimental group sample of 85 municipalities. Municipalities that did not meet these inclusion criteria were excluded.

### Randomization and interventions

We use a verifiable and replicable block randomization procedure based on publicly available state lottery numbers. The chosen method had to meet two major constraints. First, it had to be sufficiently simple that the ASF could explain, justify, and replicate the randomization mechanism to Congress. Second, the randomization process had to be compatible with the operational and technological infrastructure of the implementing agency (effectively limiting software solutions to Microsoft Excel). The experimental group consists of 17 blocks with 5 municipalities each. Using non-uniform random assignment and a 1:1:3 blocking ratio we assigned one municipality per block to be audited by the ASF, another by the EFSL of the block’s state, and the remaining three municipalities to the control condition (no intervention). Specifically the block randomization process proceeded as follows: By state, we provided each municipality with a pair of single-digit “tickets”:Block municipalities by stateIn Excel list municipalities in increasing order based on their individual identifier provided by the Mexican National Institute of Statistics and Geography (INEGI, in Spanish).Assign each municipality two single-digit “tickets”, and do this sequentially for all municipalities (e.g. 0-1, 2-3, 4-5, 6-7, 8-9 …).We generated a random vector of “winning digits”:To generate the random “winning digits”, we used the winning numbers of the seven largest prizes of the Mexican National Lottery of the first Tuesday of March 2011.Each winning number has 5-digits.We ordered the 5-digit winning numbers in decreasing order of prize.Our first five “winning digits” come from the number associated with the highest prize (e.g. for the date we used, the number was 23862 and the price 5 million pesos), the next ten “winning digits” digits come from the second and third prizes.The fourth largest prize (of 80,000 pesos) was won by four numbers. To order these tied lottery numbers randomly, we (1) ordered the numbers in increasing order; (2) grab the number associated with the largest prize in the lottery of 22 February (e.g. number 36625), delete one repeated digit (e.g. becomes 3625); (3) assign one of these digits to each of the four tied lottery numbers; (4) use this assigned digit to sort the four tied lottery numbers in increasing order (e.g. 2,3,5,6).Concatenating the 15 “winning digits” from three lottery numbers associated with the three top prizes, and the random ordering of the four lottery numbers tied for fourth prize, gives us a random vector of 35 “winning digits”, enough to randomly assign 17 municipalities to ASF audit, and 17 municipalities to EFSL audit.We then assigned municipalities to treatment arms based on the random vector of “winning digits”:Start reading from the top of the vector of “winning digits”. The first winning digit is a 2, so assign the municipality in the first state holding the single-digit “ticket” 2 to an ASF audit. Then, use the second “winning digit” from the vector to assign a municipality in the second state to ASF audit, and so on for all 17 states.Repeat the procedure – starting from the 18^th^ element of the vector of winning digits – to allocate one municipality by each of the seventeen states to an audit by the EFSL.Municipalities not allocated to EFSL or ASF serve as control.

A worked example of the randomization procedure is provided in Table 2. The process of randomization was carried out by the researchers (AO and FM) and approved and implemented by the ASF in collaboration with the EFSL.

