**PANEL B: randomization of municipalities**						
**ID**	**State**	**Municipality**	**FISM transfer (millions)**	**“Ticket” Digits**	**ASF**	**EFSL**
07022	Chiapas	Comitán de Domínguez	69	0-1		
07028	Chiapas	Chenalhó	61	2-3	1	
07076	Chiapas	Ocozocoautla de Espinosa	68	4-5		1
07092	Chiapas	San Cristóbal de Las Casas	65	6-7		
07111	Chiapas	Tecpatán	59	8-9		
08012	Chihuahua	Carichí	12	0-1		
08021	Chihuahua	Delicias	15	2-3	1	
08030	Chihuahua	Guazapares	11	4-5		
08032	Chihuahua	Hidalgo del Parral	13	6-7		
08066	Chihuahua	Uruachi	13	8-9		1

The sequence of random numbers from Panel A is: 23862, 19186, 54595, 42585, 02437, 45776, 09502. We use the first 17 winning digits to allocate one municipality by state to an audit by ASF. For example, the first winning digit in the random sequence is a 2. Because Chenalhó was allocated that “ticket” (see Panel B, Digits column), it is selected to be audited by ASF. The second winning digit in the random sequence is a 3, and so Delicias is selected, and so on for the remaining 15 states. To allocate EFSL we begin at the top again, starting with the 18^th^ digit in the random sequence, a 5. Accordingly, Ocozocoautla de Espinosa is allocated to EFSL, and so on. Had the 18^th^ digit been a 2 or a 3, we would have skipped that digit, moved to the next digit different from 2 or 3, and used that digit to allocate the first municipality to EFSL. One municipality cannot be assigned to both ASF and EFSL.

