The method of randomization adopted is transparent, replicable, and verifiable. In addition, the only software requirements are a web browser (to access the lottery numbers) and Microsoft Excel. These features were key for the ASF to accept the procedure. However, the lottery numbers span the range 00000 to 59999. Accordingly, the first digit of every winning lottery number can only take the values 0 through 5 while all other digits that can take values from 0 to 9. Thus, the fourth and fifth municipalities in the first state of our study have in practice zero chance of being audited by the ASF because they hold “tickets” (6,7) and (8,9) respectively. After the first assignment, this happens every fifth assignment, when a new lottery number is added to the sequence of “winning digits”. In other words, the randomization procedure generates known non-uniform probabilities of treatment in a subset of the blocks. Only 4 assignments to ASF and 3 to EFSL are affected by the non-homogeneous randomization. Even so, because the probabilities of assignment are known exactly we can adjust randomization hypothesis tests and use inverse probability weighting for estimates. Municipalities assigned to an audit are audited as usual by the assigned federal or state auditor [42]. Figure 1 provides a schematic layout of a municipal FISM audit process.

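### The tie-break for the four 80,000-peso numbers is random but not uniform, so the assignment probabilities are not those implied by the 0-5 leading digit alone

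*Protocol article*

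**What the plan says.** All references are to the section Randomization and interventions of the protocol article, including Table 2 and the paragraph after it.

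- **Source of the digits:** "we used the winning numbers of the seven largest prizes of the Mexican National Lottery of the first Tuesday of March 2011". Seven five-digit numbers give 35 digits. The first 17 assign ASF audits, one per state. EFSL audits are assigned "starting from the 18^th^ element of the vector of winning digits".
- **The tie:** "The fourth largest prize (of 80,000 pesos) was won by four numbers". The procedure is "To order these tied lottery numbers randomly, we (1) ordered the numbers in increasing order", then "grab the number associated with the largest prize in the lottery of 22 February (e.g. number 36625), delete one repeated digit (e.g. becomes 3625", attach one of these digits to each tied number, and "use this assigned digit to sort the four tied lottery numbers in increasing order".
- **The result, in the note to Table 2:** "The sequence of random numbers from Panel A is: 23862, 19186, 54595, 42585, 02437, 45776, 09502". The same note adds the skip rule: a digit pointing to the municipality already assigned to ASF is passed over for the next one.
- **Non-uniformity, in the paragraph after Table 2:** lottery numbers run from 00000 to 59999, so a leading digit can only be 0 to 5. Four ASF and three EFSL assignments are said to be affected. The paragraph continues: "Even so, because the probabilities of assignment are known exactly we can adjust randomization hypothesis tests and use inverse probability weighting for estimates". The tie-break is not mentioned there.

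**The concern.** Sorting by size is harmless if a uniform random permutation follows, because the leading digit of each tied number is then again uniform on 0-5. The permutation used here is not uniform, for two reasons. The February number comes from the same kind of draw, so its own first digit is capped at 5. That digit is attached to the smallest tied number, which is therefore pulled towards the front. Also, the February number was public a week before the 1 March draw. If it is held fixed, the order by rank is fixed too, and the leading digits behave as order statistics.

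The article rests both its randomization tests and its inverse probability weights on exact assignment probabilities, but gives only one cause of non-uniformity. An analyst who works from that cause alone would use the wrong probabilities in the blocks served by the tied numbers. With 17 ASF and 17 EFSL municipalities, each weight counts.

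**Working it through.** **Inputs.** Tied numbers 02437, 09502, 42585, 45776; keys 3, 6, 2, 5 (Table 2); range 00000-59999; EFSL starts at digit 18; skip rule from the note to Table 2. Assumptions: numbers are uniform on the stated range, the February draw has the same range and is independent of the March draw, and a skipped digit is used up.

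**1. Reproducing the article's figures.** Sorting the tied numbers by key gives 42585, 02437, 45776, 09502, as printed. By size these are ranks 3, 1, 4, 2. Leading digits sit at positions 1, 6, 11, 16, 21, 26 and 31. Four fall within the first 17 (ASF) and three after it (EFSL), which matches the stated count. The tied numbers supply positions 16, 21, 26 and 31.

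**2. Benchmark.** Under a uniform order each pair 0-1, 2-3, 4-5 has probability 1/3 at a leading digit.

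**3. February number held fixed.** For rank k of four, P(X(k) ≤ x) = Σ(j = k to 4) C(4,j) x^j (1−x)^(4−j), with x = 1/3 for pair 0-1 and x = 2/3 for digits 0-3.

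Rank 3 (position 16):
- Pair 0-1: 4(1/3)³(2/3) + (1/3)⁴ = 9/81 = 0.111.
- Digits 0-3: 4(2/3)³(1/3) + (2/3)⁴ = 48/81, so pair 2-3 has 39/81 = 0.481.
- Pair 4-5: 33/81 = 0.407.

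Rank 1 (position 21): 1 − (2/3)⁴ = 65/81 = 0.802 for pair 0-1, 15/81 = 0.185 for 2-3, and 1/81 = 0.012 for 4-5. Ranks 4 and 2 (positions 26 and 31) mirror ranks 1 and 3.

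**4. February number redrawn.** Of 60,000 possible numbers, 30,240 (50.4%) have exactly one repeated pair, so that deleting one copy leaves four distinct keys. Among these, the smallest tied number comes first with probability 0.349 (first copy deleted) or 0.415 (last copy deleted), not 0.25. The other three ranks share the rest equally, at 0.217 or 0.195 each. The probabilities of pair 0-1 over ranks 2 to 4 sum to (33 + 9 + 1)/81 = 0.531. Pair 0-1 at position 16 is then 0.349 × 0.802 + 0.217 × 0.531 = 0.395, or 0.415 × 0.802 + 0.195 × 0.531 = 0.436.

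**5. The ASF draw in state 16** (position 16; no skip rule applies):

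| Order | Pair 0-1 | Pair 2-3 | Pair 4-5 |
|---|---|---|---|
| Uniform | 0.333 | 0.333 | 0.333 |
| February fixed | 0.111 | 0.481 | 0.407 |
| February redrawn | 0.395-0.436 | 0.301-0.314 | 0.263-0.291 |

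The realised digit is 4. The ASF weight is 1/0.407 = 2.5 (fixed) or 1/0.291 to 1/0.263 = 3.4 to 3.8 (redrawn), against 3.0.

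**6. EFSL draws under the full rule.** Reading the printed vector with skips, positions 21, 26 and 31 serve states 4, 8 and 10. In 300,000 simulated runs they did so in only 41%, 27% and 12% of runs, so digit-level figures are diluted. The EFSL probability of the realised ticket was:

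| State (ticket) | Uniform order | February fixed | February redrawn |
|---|---|---|---|
| 4 (0-1) | 0.25 | 0.45 | 0.27-0.28 |
| 8 (4-5) | 0.24 | 0.35 | 0.24-0.25 |
| 10 (0-1) | 0.21 | 0.22 | 0.20 |

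**7. The count of affected assignments.** It holds only if skips are ignored. First, skips spread positions 21, 26 and 31 over several states. Second, a restricted ASF draw alters the EFSL draw in the same state. In state 1, tickets 6-7 and 8-9 can never be the ASF municipality, so each has EFSL probability 1/4 = 0.25. The other three pairs have 2/3 × 1/4 = 0.167. An unrestricted block gives 0.20. Third, with February fixed, the second digits at positions 22 and 27 run from 0.15 to 0.26 per pair against 0.20.

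**8. Running out of digits.** With skipped digits used up, the printed vector assigns state 13 with digit 35 and leaves nothing for states 14 to 17, although the article calls 35 digits enough.

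**The case against.** The strongest reply is that the February number is itself a public lottery draw, and the ascending sort merely labels the tied numbers before it permutes them. This stands. A reader might infer that the ordering was not random at all. The documents do not support that: if the rule was set before 22 February, the order is random but not uniform. Nor do they support an inference that the rule was chosen with the March numbers in view, because they do not say when it was set.

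A reader might also take the 0.80 at positions 21 and 26 as a municipality's probability, giving a weight of 1/0.80 = 1.25 instead of 3. This fails too. Neither figure is any municipality's EFSL weight under the full rule. In state 4 the weights are about 1/0.45 = 2.2 against 1/0.25 = 4.0.

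A third reply is that the article discloses the rule and flags these draws as non-uniform, prints no probabilities within 0-5, and leaves computation to an analytical plan that is not shown. That is fair: the 1/3 is what the stated cause implies, not a printed figure. But flagging a draw for one reason does not give its probability when a second cause is left out.

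Finally, the rule for deleting a repeated digit is incomplete in general, but it was used once, on 36625, where either 6 can go. It matters only if the February number is redrawn.

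**Conclusion.** The point holds in a limited form. Randomization took place and the printed order reproduces exactly. What is wrong is the description of the order as random without qualification, the single cause given for non-uniformity, and the count of four ASF and three EFSL assignments.

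The clearest case is the ASF draw in state 16, which departs from 1/3 on either view of the February number. For EFSL the realised-ticket shift is large in states 4 and 8 with February fixed, small with it redrawn, and negligible in state 10 either way. The point therefore concerns a few of 17 blocks and does not threaten the trial as a whole.

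The sizes rest on the assumptions listed in the working. If skipped digits were not used up, the EFSL figures would differ, while those for state 16's ASF draw would not. Whether an analysis is actually affected depends on how the probabilities are computed, which the article does not show.

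**What to change.** 1. Replace the unqualified claim of random ordering with a description of what was done, and state whether the rule was set before or after the 22 February draw.
2. Derive each municipality's ASF, EFSL and control probability, and the reference distribution for the randomization tests, by simulating the complete rule actually applied: seven numbers from 00000-59999, the sort, the February key, the skips, and whatever was done when the 35 digits ran out. Do not build them from a leading digit of 0-5 and other digits of 0-9.
3. Hold the February number fixed in the main analysis. This is valid whether the rule was set before 22 February or between the two draws. Redraw it as a sensitivity analysis, stating which copy of a repeated digit is deleted and how numbers without exactly one repeated pair are handled.
4. Correct the statement that only four ASF and three EFSL assignments are affected.

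The cost is a short simulation, a few sentences of text, and slightly more variable weights in a few blocks. No new data are needed, and the article describes analysis as still under way.

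### The article does not say where digit-reading resumes after a skip: read sequentially, the 35 lottery digits run out after state 13, and at fixed positions two digits each decide two states, so the EFSL allocation and its probabilities are not reproducible as printed

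*Protocol article*

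**What the plan says.** The Randomization and interventions section concatenates seven five-digit lottery numbers into a vector of 35 digits and calls it "enough to randomly assign 17 municipalities to ASF audit, and 17 municipalities to EFSL audit". Each block of five municipalities receives the ticket pairs 0-1, 2-3, 4-5, 6-7 and 8-9.

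The Table 2 footnote prints the digits: "The sequence of random numbers from Panel A is: 23862, 19186, 54595, 42585, 02437, 45776, 09502". It then says: "We use the first 17 winning digits to allocate one municipality by state to an audit by ASF". The EFSL pass repeats the procedure "starting from the 18^th^ element of the vector of winning digits". If the first EFSL digit had hit the ASF municipality, "we would have skipped that digit, moved to the next digit different from 2 or 3, and used that digit" for the first EFSL assignment.

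The skip is described for the first state only. Neither place says which digit the next state reads after a skip, or what happens if the vector ends. The same section states that the assignment probabilities are known exactly and relies on them to adjust the randomization tests and for inverse probability weighting. The abstract and the conclusion present the randomization as verifiable and replicable.

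**The concern.** Eighteen digits for 17 draws leave one spare, while each digit has about a one-in-five chance of hitting the ASF municipality. On the plain sequential reading, the stated sufficiency is therefore not a property of the rule, and the printed digits can be used to test it.

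The mechanism is the basis of inference here. The Statistical methods section relies on randomization tests with known probabilities, and the weights come from the same source. If the EFSL rule is not determined by the text, a reader cannot rebuild the EFSL allocation, its probabilities or the reference distribution for contrasts that involve the EFSL arm (EFSL against control, pooled audit against control, ASF against EFSL).

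**Working it through.** **Inputs.** The printed sequence (Table 2 footnote) has 7 × 5 = 35 digits. ASF digits, positions 1 to 17: 2 3 8 6 2 1 9 1 8 6 5 4 5 9 5 4 2. Digits left for EFSL, positions 18 to 35: 5 8 5 0 2 4 3 7 4 5 7 7 6 0 9 5 0 2. A conflict occurs when the EFSL digit falls in the same ticket pair as the state's ASF digit.

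**The article's own example.** For states 1 and 2, the ASF digits 2 and 3 select tickets 2-3 in both, and the EFSL digits 5 and 8 select tickets 4-5 and 8-9. This matches Table 2, Panel B. Sorting the four tied numbers by 3, 6, 2, 5 also gives the printed order.

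**Replay of all 17 states.** Entries are position (digit). *Sequential*: a skipped digit is discarded and the next state reads the next unread digit. *Fixed*: state k starts at position 17 + k and borrows a later digit only on conflict.

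| State | ASF digit | Sequential | Fixed | Same municipality? |
|---|---|---|---|---|
| 1 | 2 | 18 (5) | 18 (5) | yes |
| 2 | 3 | 19 (8) | 19 (8) | yes |
| 3 | 8 | 20 (5) | 20 (5) | yes |
| 4 | 6 | 21 (0) | 21 (0) | yes |
| 5 | 2 | skip 22; 23 (4) | skip 22; 23 (4) | yes |
| 6 | 1 | 24 (3) | 23 (4) | no |
| 7 | 9 | 25 (7) | 24 (3) | no |
| 8 | 1 | 26 (4) | 25 (7) | no |
| 9 | 8 | 27 (5) | 26 (4) | yes |
| 10 | 6 | skip 28, 29, 30; 31 (0) | 27 (5) | no |
| 11 | 5 | 32 (9) | 28 (7) | no |
| 12 | 4 | skip 33; 34 (0) | 29 (7) | no |
| 13 | 5 | 35 (2) | 30 (6) | no |
| 14 | 9 | none left | 31 (0) | – |
| 15 | 5 | none left | 32 (9) | – |
| 16 | 4 | none left | skip 33; 34 (0) | – |
| 17 | 2 | none left | 34 (0) | – |

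Sequential: 13 assignments plus 5 skips use all 18 digits. Fixed: 17 assignments and 2 skips, with digits 23 and 34 each used twice. The readings differ in 7 of the 13 states that both assign. The names of states 3 to 17 are not printed, but conflicts depend only on digit positions.

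A third reading, in which a skipped digit is held over for the next state, also completes all 17. It differs from the fixed reading in states 6 and 17 (digits 22 and 33 in place of 23 and 34).

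**Chance that the vector lasts.** With a conflict chance of 0.2 per digit:

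- Sequential: P(18 digits suffice) = 0.8^17 + 17 × 0.2 × 0.8^17 = 0.8^17 × 4.4 = 0.099. Exhaustion is therefore about 90%; simulation with first digits limited to 0-5 agrees. Expected total need is 17 + 17/0.8 = 38.25 digits.
- Fixed: state 17 fails if digits 34 and 35 both conflict (0.2² = 0.04), and state 16 if 33 to 35 all do (0.2³ = 0.008). Earlier states add little and overlaps subtract a little. Simulation gives about 4.7%.

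**Effect on probabilities: state 4, tickets 6-7 or 8-9, before the draw.**

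- Fixed: position 21 is the first digit of a lottery number, so it can only be 0-5. Tickets 6-9 are reached only after a skip. P(skip) = 3/5 × 1/3 = 0.2, and each of the four remaining municipalities then has 1/4, so 0.2 × 0.25 = 0.05 each.
- Sequential: state 4 starts at position 21 only if states 1 to 3 had no skip (0.8³ = 0.512). Otherwise it nearly always starts on an unrestricted digit, with probability about 0.2. This gives about 0.512 × 0.05 + 0.488 × 0.2 = 0.12 each.

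For the municipality actually drawn in state 4 (tickets 0-1), the probabilities are about (1 − 2 × 0.12)/3 = 0.25 against (1 − 2 × 0.05)/3 = 0.30, so its weight is about 4.0 against 3.3.

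**The case against.** The best defence is that repeating the ASF procedure from the 18th element means one fixed position per state, as in the ASF pass. On that reading all 17 EFSL assignments finish by digit 34, the worked example is reproduced, and 35 digits did suffice for this draw. The article also counts three EFSL assignments affected by restricted first digits. Positions 21, 26 and 31 are exactly three, whereas wrapping to the top or adding an eighth lottery number would put state 14 on a fourth. Finally, the article nowhere says that its tests permute blocks independently, and Additional file 2, which is not shown, may record the rule.

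Much of this stands. A reader might infer from the sequential trace that four of the 17 EFSL assignments had no random source, that the weights and tests are wrong, or that four units should be dropped. The documents support none of these. The four-state shortfall and the 90% figure belong to one reading, and a shared digit still leaves marginal probabilities that can be computed by re-running the rule.

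The defence does not settle which rule was used. The sequential trace uses the same three first-digit positions before it runs out, so the count of three argues against an added lottery step but does not identify fixed positions. The fixed reading itself ties state 5 to state 6 and state 16 to state 17, which the article does not mention.

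**Conclusion.** The point holds as a defect in the stated EFSL mechanism. The text admits at least two rules. One exhausts the printed vector after state 13 and would do so in about 90% of draws; the other completes it by letting two digits decide two states each, and would run out in about 5% of draws. They yield different municipalities in 7 of 13 comparable states and different assignment probabilities, for example 0.12 against 0.05. As printed, the claims of replicable randomization and exactly known probabilities therefore do not hold for EFSL.

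This rests on the printed digits and ticket pairs and, for the draw probabilities, on equally likely digits with first digits limited to 0-5. How the actual allocation was completed cannot be told from the article. ASF assignment uses digits 1 to 17 with no skips and is unaffected.

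**What to change.** 1. Correct the sufficiency sentence. State where reading resumes after a skip, and what was done if the digits ran out.
2. List the digit position used for each of the 17 EFSL assignments.
3. Code that exact rule, with first digits limited to 0-5. Obtain all EFSL assignment probabilities, the inverse probability weights and the randomization-test reference distribution by re-running it, not by permuting blocks independently.
4. Only if the authors find that some blocks had no lottery digit, show the results with and without those whole blocks as a sensitivity analysis, and limit the replicability claim to the others.

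The cost is one corrected paragraph, a 17-row list and a short simulation script. No new data are needed.
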